## Abstract

**Background:**

Shoulder instability is a common problem affecting young adults. Stabilization surgery followed by physiotherapy rehabilitation has been shown to reduce the chance of further episodes of shoulder dislocation and to improve quality of life in patients who sustain a shoulder dislocation as a result of a high collision trauma, but it is unclear if surgical intervention is beneficial for patients with atraumatic shoulder instability who have structural damage at the shoulder. The aim of this randomized controlled clinical trial is to determine if the addition of surgical intervention to physiotherapy rehabilitation improves outcomes for patients with atraumatic shoulder instability who have sustained soft tissue damage at their joint.

**Methods/Design:**

140 participants will be recruited. Patients with feelings of insecurity (apprehension) at their shoulder joint, which is not the result of a collision injury, with physical signs of shoulder joint instability will be invited to participate. Consenting participants will undergo arthroscopic investigation of the shoulder joint. Patients with capsulolabral damage will be randomly allocated using a concealed allocation procedure to either stabilization surgery immediately following the arthroscopic examination or no additional surgical procedure. All participants will then receive the same postoperative physiotherapy protocol for up to 6 months. Outcomes (pain, functional impairment and number of shoulder dislocations sustained) will be evaluated prior to surgery and, together with participant-reported improvement, again at 6, 12 and 24 months after randomization. The primary endpoint will be pain and functional impairment at 2 years. Participants, clinical staff (but not surgeons) and assessors will be blind to whether stabilization surgery was performed. Data analysis will be conducted on an intention-to-treat basis with the focus on estimation of the effect.

**Discussion:**

This trial will have a direct and immediate impact on clinical decision making by establishing if patients presenting with soft tissue shoulder damage associated with atraumatic shoulder instability should be referred for stabilization surgery before commencing physiotherapy rehabilitation in order to ensure optimal outcome. This in turn will ensure effective, efficient use of scarce health resources to manage this common often disabling musculoskeletal condition.

**Trial registration:**

Study was registered with National Institutes of Health Clinical Trials Protocol Registration System in December 2012.

ClinicalTrials.gov Identifier: NCT01751490.

## Background

The shoulder is the most mobile joint in the body and the joint most susceptible to instability. More than any other joint, the shoulder relies on dynamic muscle support to achieve functional stability [1].

Shoulder instability is defined as symptomatic, abnormal motion at the shoulder (glenohumeral) joint. It can result in a spectrum of symptoms including pain, a feeling of insecurity, and dislocation [2]. Shoulder instability is a common problem predominantly occurring in the younger population [3]. Patients suffering from shoulder instability experience significant reduction in ability to function physically, socially and emotionally [4]. The resulting decrease in quality of life ranks in severity with major medical conditions such as hypertension, congestive cardiac failure, acute myocardial infarction, diabetes mellitus and clinical depression [4].

Shoulder instability can occur as a result of shoulder trauma, e.g. following dislocation (traumatic instability) or it can develop without a traumatic episode (atraumatic instability). A combination of factors can result in shoulder instability: damage to the joint (e.g. bony Bankart lesion of the glenoid fossa, Hills Sachs lesion of the humeral head); damage to the capsulolabral complex (e.g. tears/detachment of the glenoid labrum, joint capsule or ligaments); and loss of dynamic muscle control. Treatment for shoulder instability consists of surgery to repair bony and capsulolabral damage and physiotherapy to restore muscle control mechanisms. However, few high quality randomized controlled clinical trials have investigated which combination of operative and non-operative treatment affords the most effective outcome for patients presenting with shoulder instability.

Management of shoulder instability typically consists of a combination of immobilization in supportive slings, surgical intervention to repair or tighten damaged capsular, ligamentous and/or labral structures in the shoulder joint, and physiotherapy rehabilitation including strengthening exercises [5] and exercises to restore normal dynamic stabilization mechanisms at the shoulder. Currently, the management of shoulder instability differs depending on the precipitating factors. Operative intervention followed by physiotherapy rehabilitation is the preferred option for instability that has occurred as a result of trauma. Non-operative/conservative treatment is preferred as the initial management of atraumatic instability [6]. However, these practices are not based on rigorous evidence. Few high quality randomized controlled clinical trials have investigated which combination of operative and non-operative treatment affords the most effective outcome for patients presenting with shoulder instability.

Evidence from one randomized controlled clinical trial [7] and several prospective cohort studies [8–10] comparing surgery followed by rehabilitation to rehabilitation alone provides consistent support in favour of operative intervention in patients following a traumatic primary shoulder dislocation resulting in bony and/or capsulolabral damage. Two to three years after injury young adults (<30 years of age) who had received the surgical option demonstrated significant reduction in re-dislocation rate [7, 10] and a small but clinically significant improvement in quality of life scores [7]. In addition, young military cadets demonstrated a significant reduction in the development of recurrent instability [8, 9].

No randomized clinical trials or prospective cohort studies have compared operative and non-operative treatment in the management of atraumatic shoulder instability. Evidence from retrospective observational studies suggests that both surgical and non-surgical treatment may be effective. Several studies indicate that an excellent outcome can be achieved with specialist physiotherapy treatment for atraumatic shoulder instability [11, 12]. Other studies indicate that surgery is as effective for atraumatic as for traumatic instability [13, 14], can result in a decreased shoulder dislocation recurrence rate [15] and can result in improvement in function, stability and motion [16].

On the other hand, some studies indicate that surgery is not successful for the treatment of atraumatic shoulder instability and can result in longer term detrimental effects. A small prospective observational study did not find significant functional improvement in young athletes with multidirectional instability following surgery [17] and failure rates of up to 60% have been reported following thermal capsulorraphy surgery [18]. In addition, there is some evidence that patients who have undergone unsuccessful surgery for atraumatic instability and subsequently proceed with conservative rehabilitation have worse outcomes than those who are initially treated conservatively [6]. It has also been suggested that in younger patients whose atraumatic instability is primarily due to abnormal, unbalanced muscles forces on the shoulder joint surgical intervention may contribute to early degenerative changes. [19, 20].

In summary, the limited evidence available suggests that, in patients with traumatic shoulder instability, surgical intervention followed by physiotherapy rehabilitation is the most effective management strategy but in patients with atraumatic instability without structural damage to shoulder capsule or ligaments, surgery is not helpful or detrimental. The role of surgical intervention in patients with atraumatic shoulder instability associated with capsulolabral damage is still unclear. A robust clinical trial is required to determine if surgical intervention is necessary to provide optimal short, medium and longer term outcomes for these patients.

### Study objectives

The aim of this randomized controlled clinical trial is to determine whether surgical intervention followed by physiotherapy rehabilitation improves pain and functional impairment outcomes in patients suffering from atraumatic shoulder instability associated with capsulolabral damage, compared to physiotherapy alone. We hypothesized that the patients receiving stabilization surgery followed by post-operative physiotherapy rehabilitation would have significantly greater short and long term improvement in pain and function.

## Methods/Design

### Design

A two-arm, double-blind randomized controlled clinical trial will be conducted. 140 patients will be recruited in two study centres and will undergo a clinical assessment to assess potential eligibility for the study. Potentially eligible patients who consent to participate will undergo arthroscopy and those with arthroscopic evidence of capsulolabral damage will be randomly allocated during the procedure into one of two groups: a *stabilization surgery* group and a *control* group. The primary outcome (pain and functional impairment) and secondary outcomes (participant-reported improvement and number of shoulder dislocations sustained) will be evaluated at baseline and 6, 12 and 24 months after randomization. Additional secondary outcomes of shoulder rotation range of motion and strength will be evaluated at 6 months after randomization. Ethics approval to conduct this study has been granted by the NRES Committee London-Stanmore and NRES Committee Wrightington, Wigan and Leigh.

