### Participants

Patients over 18 years of age of all activity levels will be eligible to participate if they report insecurity (apprehension) at the shoulder joint, have physical signs of shoulder instability (provocation of apprehension with drawer and apprehension tests), and have evidence of capsulolabral damage in the shoulder joint on arthroscopic examination. Damage to the capsulolabral complex includes any splits, fraying or detachment of any region of the glenoid labrum including the superior labrum. Patients will be excluded if they have a history of a high collision shoulder injury precipitating their apprehension symptoms, evidence of bony injury around the glenoid rim and/or humeral head or rotator cuff tear on arthroscopic examination, neural damage affecting the upper limb, or previous shoulder surgery. Prior physiotherapy treatment will not exclude eligible patients from participating in this clinical trial.

Potential participants will be identified from patients attending clinics conducted at the participating hospitals. Experienced clinicians in these clinics will inform potential participants of the clinical trial and provide them with information regarding the trial in the form of a written information sheet. With the patient’s permission this clinician will forward contact information to the research team. An experienced research assistant, who will be a registered health professional, will contact the potential participant to discuss the purpose of the study and to answer any questions this patient may have regarding the study. The research assistant will them seek written consent from those who volunteer to participate.

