### Interventions

140 participants will be recruited and randomly allocated to either a:stabilization surgery group (70 participants). Participants in this group will receive an arthroscopic investigation of the shoulder joint followed by arthroscopic stabilization surgery and postoperative physiotherapy rehabilitation.control group (70 participants). Participants in this group will receive an arthroscopic investigation of the shoulder joint followed by postoperative physiotherapy rehabilitation.

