### Sample size

The sample size was calculated assuming a 10.4% change on the WOSI given a standard deviation of 18% change, a significance level of 5% and assuming a 10% (worst-case) loss to follow-up. A 10.4% change in total WOSI score represents the minimally important change required to represent a clinically significant improvement [28]. This is a conservative sample size estimate as it ignores the additional power conferred by the longitudinal analysis that is to be used in this study.

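### The Design section counts the 140 before eligibility assessment and the Interventions section counts the same 140 as randomised; the sample-size inputs fit only the second.

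*Protocol article*

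**What the plan says.** All references are to the protocol article.

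- **Design:** "140 patients will be recruited in two study centres and will undergo a clinical assessment to assess potential eligibility for the study". The text then narrows this group. Those who look eligible and consent go to arthroscopy, and "those with arthroscopic evidence of capsulolabral damage will be randomly allocated during the procedure into one of two groups".
- **Interventions:** "140 participants will be recruited and randomly allocated to either" of two arms, each given as 70 participants.
- **Participants:** capsulolabral damage at arthroscopy is required for entry. Patients are also excluded for "evidence of bony injury around the glenoid rim and/or humeral head or rotator cuff tear on arthroscopic examination".
- **Sample size:** a 10.4% change on the WOSI, a standard deviation of 18%, a 5% significance level, and "assuming a 10% (worst-case) loss to follow-up". Neither the target power nor the sidedness of the test is stated. The section calls the estimate conservative because it leaves out the power gained from the longitudinal analysis.
- **Abstract, Methods/Design:** gives 140 recruited, then describes invitation, consent and arthroscopy, after which "Patients with capsulolabral damage will be randomly allocated using a concealed allocation procedure".

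**The concern.** One number is used at two points of the patient pathway. In the Design section it stands ahead of three filters: clinical assessment, consent and arthroscopic findings. In the Interventions section it stands after all of them. The two agree only if no one fails any filter, yet the eligibility criteria are written so that some patients can fail as late as arthroscopy.

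The number is the recruitment target. A team working from the Design section could close recruitment once 140 patients had been assessed, while a team working from the Interventions section would continue until 140 had been randomised. Under the first rule the arms would fall short of 70 by an amount the documents do not let anyone predict, and the sample-size calculation would no longer describe the trial.

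**Working it through.** **Step 1. Reproduce the 140.** Inputs from the Sample size section: difference 10.4, standard deviation 18, significance level 5%, loss to follow-up 10%. Assumed, because not stated: a two-sided test, 90% power and a two-sample comparison of means.

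- Standardised difference: d = 10.4 / 18 = 0.578.
- Evaluable per arm: n = 2 × (1.960 + 1.282)² / d² = 62.95, rounded up to 63.
- Allowing for loss: 63 / 0.9 = 70 per arm, 140 in total.

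This matches the Interventions section exactly. With the same inputs and a two-sided test, 80%, 85% and 95% power give totals of 108, 120 and 174. One-sided tests at 80%, 85%, 90% and 95% power give 86, 98, 116 and 146. A t-based calculation at two-sided 90% power gives 64 evaluable per arm, and 128 / 0.9 is about 142. Two-sided 90% power with the normal formula is therefore the natural reading of how 140 arose.

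**Step 2. See what the 140 allows for.** The whole step from 63 to 70 per arm is used up by the 10% loss to follow-up. Nothing is left for patients excluded before randomisation. The calculation therefore needs 140 randomised, not 140 assessed.

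**Step 3. Illustrate the other reading.** Suppose 140 patients enter and a share *e* is lost before randomisation by any route. The documents give no value for *e*; the values below are assumptions.

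- Randomised = 140 × (1 − e).
- Evaluable per arm = 0.9 × randomised / 2.
- Normal-approximation power = Φ(d × √(n/2) − 1.960). The t-based figure uses the noncentral t distribution.

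| Lost before randomisation | Randomised | Evaluable per arm | Power, t-based | Power, normal |
|---|---|---|---|---|
| 0% | 140 | 63.0 | 89.6% | 90.0% |
| 10% | 126 | 56.7 | 86.2% | 86.8% |
| 20% | 112 | 50.4 | 81.9% | 82.7% |
| 30% | 98 | 44.1 | 76.5% | 77.4% |

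Power of 80% (normal approximation) needs 47.02 evaluable per arm, which is 2 × 47.02 / 0.9 = 104.5 randomised, or about 75% of 140.

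All of these figures are for an unadjusted two-sample comparison. The planned analysis adjusts for baseline and uses mixed models over 6, 12 and 24 months. The article gives no correlations from which that gain could be calculated.

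**The case against.** The best defence is that the document already settles the matter. The Interventions section is explicit about allocation and arm sizes, the sample-size inputs agree with it, and no figure is miscalculated. On this view the Design section merely uses the word recruited loosely. Much of this stands: 140 randomised is very probably what was meant, and the sample size itself is not in error. It does not remove the conflict, because the Design sentence explicitly places the 140 ahead of eligibility assessment.

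Four stronger readings are tempting, and the documents do not support them.

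- *The trial as planned is underpowered.* Nothing in the article says that recruitment stops at 140 assessed or consented. The lower power figures are conditional on that rule and on exclusion rates chosen for illustration. Damage is defined broadly, to include fraying or splitting of any part of the labrum, so the article gives no reason to expect that many patients will fail on that criterion.
- *There is no reserve at all.* The Sample size section says that its estimate ignores power from the longitudinal analysis and calls the 10% loss a worst case. Some unquantified reserve therefore exists, and it could offset a small shortfall.
- *The Abstract repeats the error.* It gives 140 recruited and then describes the pathway. It does not place the 140 ahead of eligibility assessment and is compatible with the Interventions section.
- *The article should have given an expected exclusion rate and a number to be consented.* A condensed article commonly leaves such detail to the full protocol, so its absence is not a fault here.

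**Conclusion.** The contradiction is real and lies in the text: the Design and Interventions sections attach the same 140 to different stages. The sample-size inputs decide between them. With two-sided 90% power assumed they give 70 per arm after loss to follow-up and nothing more, so 140 has to be the number randomised, and the Design section misstates the target.

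If recruitment followed the Design section, the stated arm sizes would not be reached as soon as anyone was excluded or declined. The size of the effect cannot be fixed from the documents. As an illustration, losing 10% to 30% would take unadjusted power from about 90% to between about 86% and 77%, and power would stay near 80% as long as about three-quarters of the 140 were randomised. The conclusion about which number is right rests on the inferred power and sidedness, and on the exact match with the stated arm sizes.

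**What to change.** In the Design section, define 140 as the number randomised, 70 per arm, and state that recruitment continues until that number is reached. The text should then acknowledge that more than 140 patients will be assessed and undergo arthroscopy, unless nobody is excluded. Aligning the Abstract would help clarity.

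If 140 is truly the number entering assessment, the correction goes the other way: replace the 70 per arm in the Interventions section with the expected number randomised, and restate the sample-size justification for that smaller number.

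The first option costs only a change of wording. It leaves the planned sample size, arms and analysis untouched, but makes explicit that the number undergoing arthroscopy is expected to exceed 140. The second requires the sample-size section to be reworked.

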### Participants

Patients over 18 years of age of all activity levels will be eligible to participate if they report insecurity (apprehension) at the shoulder joint, have physical signs of shoulder instability (provocation of apprehension with drawer and apprehension tests), and have evidence of capsulolabral damage in the shoulder joint on arthroscopic examination. Damage to the capsulolabral complex includes any splits, fraying or detachment of any region of the glenoid labrum including the superior labrum. Patients will be excluded if they have a history of a high collision shoulder injury precipitating their apprehension symptoms, evidence of bony injury around the glenoid rim and/or humeral head or rotator cuff tear on arthroscopic examination, neural damage affecting the upper limb, or previous shoulder surgery. Prior physiotherapy treatment will not exclude eligible patients from participating in this clinical trial.

Potential participants will be identified from patients attending clinics conducted at the participating hospitals. Experienced clinicians in these clinics will inform potential participants of the clinical trial and provide them with information regarding the trial in the form of a written information sheet. With the patient’s permission this clinician will forward contact information to the research team. An experienced research assistant, who will be a registered health professional, will contact the potential participant to discuss the purpose of the study and to answer any questions this patient may have regarding the study. The research assistant will them seek written consent from those who volunteer to participate.

### Interventions

140 participants will be recruited and randomly allocated to either a:stabilization surgery group (70 participants). Participants in this group will receive an arthroscopic investigation of the shoulder joint followed by arthroscopic stabilization surgery and postoperative physiotherapy rehabilitation.control group (70 participants). Participants in this group will receive an arthroscopic investigation of the shoulder joint followed by postoperative physiotherapy rehabilitation.

#### Arthroscopic examination

All potentially eligible patients will undergo arthroscopic examination of the shoulder under general anaesthetic. Arthroscopy is the gold standard for diagnosing subtle capsulolabral lesions at the shoulder [21, 22]. The patient will be prepped and draped on the operating table in the beach chair position. A 1 cm incision will be made over the back of the shoulder joint and a metal trochar used to penetrate the joint capsule. An arthroscope will be introduced into the joint. Another 1 cm incision will be made over the anterior aspect of the joint and a metal probe introduced into the joint to palpate and move intra-articular structures in order to fully assess the joint. The arthroscope will then be replaced through the front of the joint in order to visualize the posterior joint structures.

Following confirmation that the patient is eligible to participate in the trial surgery theatre staff will open a pre-prepared sealed envelope identifying group allocation for each participant and inform the surgeon if stabilization is to proceed. To ensure blinding of the participants, physiotherapy staff associated with post-operative care and research assistants, the surgeon and theatre staff will be asked not to reveal group allocation (i.e., whether stabilization surgery was performed) to anyone associated with the study.

